#### Eligibility criteria

Clinicians recruited for the BRIDGE study were general internists, family physicians, and nurse practitioners who saw patients at least 20 hours per week at one of the participating study sites. The clinicians were recruited without regard to race, gender, or age. Patients had to be between the ages of 18 and 75 years and report their race or ethnicity as African American; they had to be positive on a screener for major depressive and dysthymic disorder from the CIDI [30], which identified individuals who reported two weeks or more during the last year and one week or more during the past month when they felt sad, empty, depressed, or lost interest in things they normally enjoyed. The screener was self-administered with assistance as needed at the time of the recruitment visit. In addition, screen-positive patients had to meet criteria for one-year major depression on a subsequent structured interview [30], defined as: meeting DSM-IV criteria for MDD in the past year [31]and having symptoms present for at least one week in the past month, to be considered eligible for the study. Patients were excluded if they had an acute life-threatening condition or cognitive impairment that prevented them from completing the screener; indicated they did not intend to receive care in the clinic on an ongoing basis; had no access to a telephone; were currently pregnant, breastfeeding, or less than three months postpartum; screened positive for current bereavement, lifetime mania, or current alcohol or drug abuse; did not speak English; were currently receiving specialty mental health care; or reported immigrating to the United States within the preceding five years.

#### Randomization

Randomization was stratified by study site and conducted at the clinician level with patients sequentially selected within each randomized clinician (10 patients from each clinician). Within each study site (stratum), a randomization schedule was generated through computer by the study statistician using the Moses and Oakford algorithm [32]with the block sizes of two or four randomly created in a four to one ratio. Informed consent and baseline data collection from clinicians (background questionnaire and videotaped interview with the standardized patient) were completed before participating clinicians were randomly assigned (using a blind and secure allocation by computer) to either the standard or the patient-centered intervention. At the screening visit, patients of enrolled clinicians provided oral consent to complete the screening questionnaire. Once eligibility was confirmed, written consent and screening visit data were collected. Additionally, study staff obtained permission from eligible patients to contact them several times over the next 12 months. Patients were then assigned to the standard or patient-centered intervention according to their clinicians' randomization status. The patient recruiters were blinded to the clinicians' randomization assignment during recruitment, and the patients did not know their assigned treatment status until after enrollment. Due to the behavioral nature of the interventions, blinding or masking of study participants, investigators, and depression care managers was not possible. However, interviewers who collected baseline and follow-up data from patients at six and 12 months were masked to clinician and patient intervention assignment.

### Interventions

#### Clinician interventions

The clinician interventions were developed on a model previously shown to improve treatment knowledge for primary care clinicians [33,34]. Over the course of the study's 12-month clinician intervention period, clinicians in both intervention groups received two academic detailing visits for CME credit on the clinical management of depression from a team consisting of a primary care physician and a consultation-liaison psychiatrist. The visits were delivered within a two-month period, on average, for each clinician and focused on the latest advances in depression diagnosis and assessment (visit one) as well as treatment and referral (visit two), using the MacArthur Initiative on Depression and Primary Care Toolkit for clinicians [35]. The team visited clinicians individually or as a group according to the collective preference of clinicians at each site. In addition to approximately two hours of formal training, all clinicians received a monthly newsletter with study updates and summaries of recent journal articles related to depression. Each clinician who faced difficulty with patient diagnosis, motivation to initiate treatment, adherence to treatment, or response to treatment was invited to contact his or her consultation-liaison psychiatrist. Consultative services via monthly case conferences and collaborative patient visits were offered by the study psychiatrists; however, primary care clinicians chose to contact the consultants by telephone instead.

In contrast to the more didactic format used in the standard clinician intervention, the primary care physician/psychiatrist team that delivered academic detailing to clinicians in the patient-centered intervention guided each clinician through his or her personal interactive communication skills training program in a one-on-one or small group format with other clinicians in the practice who were also assigned to this intervention. The program featured a CD-ROM containing the clinician's interview with a simulated patient at baseline, fully-analyzed using the Roter Interaction Analysis System (RIAS) [36,37]. This sophisticated coding software generated tabular and graphic analyses of the verbal components of the interview (*e.g*., functional categories of communication and proficiencies useful in improving patient involvement in decision-making about depression treatment). Clinicians were also presented with the overall ratio of clinician to patient talk as a measure of verbal dominance [38]. The RIAS is based on a four-function model of medical interviewing that includes data-gathering, rapport-building, patient education and counseling, and facilitation and patient activation [39]. There were also targeted proficiencies related to depression included in the training program: recognizing depression; evaluating patients for associated conditions and suicidal ideation; assessing functioning and coping strategies, knowledge and beliefs about depression, and treatment preferences and concerns; and eliciting a commitment to the therapeutic plan. After viewing the analysis of communication by category, the software enabled clinicians to efficiently review examples of each function and proficiency within the interview. The CD-ROM also featured a video-glossary of simulated interviews illustrating the communication skills corresponding to each category. A companion workbook introduced clinicians to the RIAS and guided them through case-based exercises for skill practice.

#### Patient interventions

The standard and patient-centered patient interventions were both designed to incorporate state-of-the-art strategies that have been proven to enhance the quality of care for depression in primary care settings. Each intervention involved extensive one-on-one follow-up with a Depression Case Manager (DCM) to assess patients' depression status and to encourage adherence to recommended treatments and exposure to educational materials. Both DCMs were social workers with clinical experience; the standard DCM was a Caucasian woman, and the patient-centered DCM was an African-American woman.

The format and schedule for DCM contact were standardized across both interventions. Enrolled patients were contacted by their DCM within a week of the baseline telephone interview to schedule a 45-minute telephone conversation. Follow-up calls at one week, two weeks, and four to six weeks assessed each patient's depression level measured by the Patient Health Questionnaire (PHQ-9) score [40]. Symptomatic patients in the acute phase received weekly calls, while asymptomatic patients in the continuation and maintenance phases were called every eight and 12 weeks, respectively. Each DCM was also available to her patients by telephone as needed throughout the duration of the 12-month intervention.

The common goals of the standard and patient-centered DCMs were to provide needs assessment (five core areas for the standard DCM, 11 core areas for the patient-centered DCM), education, and activation messages to patients (Table 1). In addition to core areas, the needs assessment touched on active coping strategies, social stressors, and social support. To increase the efficiency and effectiveness of depression care, during every follow-up call each DCM monitored symptoms, functional status, and general health of her patients. In addition, each DCM reviewed the psychotherapy, medication, and/or alternative treatment plan developed by the patient and his or her primary care clinician. A report of relevant information was prepared for the patient, primary care clinician, and/or mental health specialist after each contact.

**Table 1 T1:** Features of the BRIDGE study patient intervention

Data collected/delivered	Standard intervention	Patient-centered intervention
Needs assessment (five core assessment areas)	X	

Patient-centered needs assessment^1 ^(11 core assessment areas)[41]		X

Education and Activation	X	X

Social support/informal counseling	X	X

Standard education materials	X	

Culturally targeted education materials		X

Black mental health alliance resource list		X

Cultural information packet for MH Providers		X

^1^More in-depth individualized questioning (using Kleinman's explanatory model approach [41]) about symptoms, functional status, social support, treatment preferences compared to the standard needs assessment. Additional assessment questionswere about literacy and language, spirituality, financial concerns, and clinician relationship.

In contrast to the standard DCM, the patient-centered DCM conducted a more comprehensive needs assessment that explored the meaning of illness from the patient's perspective [41], his or her use of spirituality as an active coping strategy, and social stressors such as racial discrimination, neighborhood safety, financial burdens, stigma, health literacy, and relationships with health professionals. She then used this patient-specific information to guide her engagement and supportive counseling of the patient and provided interested patients with the names and contact information for culturally-sensitive psychotherapists.

Patients in both interventions were asked by their DCM to try at least two educational materials, which were mailed after the initial telephone conversation. The educational materials include brochures (2004 versions), books, and DVDs/videotapes. The patient-centered intervention materials were culturally targeted and included a study calendar and a nondenominational depression prayer card for patients who described themselves as spiritual. Materials provided in each intervention are shown in Table 2[42-46]. The Black and Blue video/DVD [47] was innovative in featuring actual African-American patients rather than actors, targeting barriers to treatment for African Americans identified in previous research, and incorporating the viewpoints of African-American primary care physicians, mental health professionals, and clergy. The BRIDGE study calendar offered additional reinforcement on topics such as depression in the African-American community, substance abuse, safe and effective therapy and medication, spirituality, self-help, and suicide prevention.

**Table 2 T2:** Patient education materials

	Standard intervention	Patient-centered intervention
**Communication material**		

**Book**		

How to Heal Depression [42]	X	

Chicken Soup for the African American Soul [43]		X

**Print media**		

Depression [44]	X	

Depression and African Americans [45]		X

Prayer Card		X

Real Men, Real Depression [44]	X	

Men and Depression^1 ^[44]		X

**Visual media**		

Coping with Symptoms of Depression, DVD or Video [46]	X	

Black and Blue, DVD or Video [47]		X

Calendar		X

^1^Distributed to men only

#### Data collection at baseline and over follow-up

In addition to the main outcome and process measures, baseline data were collected to describe the characteristics of study subjects and compare these characteristics between the intervention groups assigned by randomization. While the intervention status is the main predictor variable, other factors known to be predictors of depression (*e.g*., social support) and factors that might explain why the intervention did or did not work (*e.g*., clinician and patient attitudes regarding treatment) were collected. In general, we selected instruments that are brief, have been used successfully in primary care settings, and are reliable and valid in primary care clinicians and African Americans. We also collected detailed data on racial identity and other attitudes, beliefs, and experiences that might identify intra-ethnic group differences and help determine the study's external validity. We conducted telephone interviews to measure patients' depression status, attitudes regarding treatment, use of health services and experiences of care, and reactions to the interventions at six and 12 months of follow-up. Table 3 shows the variables collected from individual clinicians at baseline (pre-intervention), immediately after their in-person intervention contacts (post-intervention), and at the end of the study. Table 4 shows socio-demographic and behavioral variables, clinical measures, and health service utilization patterns collected from patients at baseline and over follow-up.

**Table 3 T3:** Schedule of data collected from primary care clinicians in the BRIDGE study

Overall data collection	Pre intervention	Post intervention
Demographics (age, gender, race, ethnicity, place of birth, residency training, board certification status, practice experience)	X	

Specialty (internal medicine or family medicine)	X	

Previous communication skills CME training	X	X

Previous mental health CME training	X	X

Readiness to change behavior re: management of depression	X	

Knowledge, attitudes, self-efficacy re: managing depression	X	

Attitudes about race^1^	X	X

Self-reported communication and PDM style	X	

Job stress and satisfaction	X	

Self-efficacy in managing adherence problems, depression, and patients from socially and culturally diverse backgrounds	X	X

**Visit level data collection**		

Videotape with simulated patient	X	

Audiotapes with 5 to 10 depressed patients		X

Visit-specific satisfaction with each patient		X

Perceptions of patients' social and behavioral characteristics		X

Use/process evaluation of CD-ROM/workbook^2^		X

Rating of intervention effectiveness		X

^1^Explicit attitudes measured at baseline before enrollment visit; implicit attitudes measured only at end of study using the Implicit Association Test (IAT).

^2^Patient-centered intervention providers only

**Table 4 T4:** Schedule of variables collected from patients in the BRIDGE study

Measurement/collection method	Enrollment visit	6 months	12 months	18 months
**Questionnaires**				

Sociodemographics	X		X	X
Age, sex, race/ethnicity, education, income, employment^1^, health insurance^1^, financial stress^¶^				

Attitudes, beliefs, and other behavioral measures	X	X	X	X
Trust in health professionals, preferred role in decision-making, depression treatment preferences, spirituality, respect, perceived involvement in care^2^, racial identity, social support, life events				

Health Status	X	X	X	X
Physical and mental, measured by MOS-SF12, CIDI^3 ^&ES-D, psychiatric co-morbidity^4^, disability days				
Healthcare Utilization	X	X	X	X
Mental healthcare utilization (receipt of antidepressant medication and/or counseling) General healthcare utilization (emergency room visits and hospitalizations)				
Healthcare Process	X	X	X	X
PDM with providers, visit-specific and overall satisfaction, satisfaction with case manager^5^, ratings of depression care management and intervention materials^6^				

**Audiotapes **(patient-provider communication)^7^	X			

CIDI = Composite International Diagnostic Interview, Depression Scale, CES-D = Center for Epidemiologic Studies Depression Scale, PDM = participatory decision making; ^1^measured at 12 and 18 months; ^2^measured only at 18 months; ^3^not measured at six months; ^4^Substance abuse, panic attacks, anxiety, and traumatic events; ^5^measured only at six and 12 months; ^6^measured only at 12 months only; ^7^collected at enrollment visit and after primary care provider intervention.

One modification to the original study protocol was made shortly after the 12-month follow-up was complete. Because the pattern of improvement differed between intervention groups at six months and 12 months of follow-up, a decision was made to extend follow-up to one additional interview at 18 months, and IRB approval was obtained to re-contact study patients. However, because outcomes assessors at 18 months were not blinded to intervention assignment, depression status at 12 months remains the study's primary outcome.

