#### Patients

On onsite recruitment days, participating clinics placed signs in registration areas that asked, 'Do you want to improve your emotional health and possibly earn up to $75?' The signs also specified which clinicians were participating in the study. During registration, patients were given a card that informed them their clinician was participating in a study to improve emotional health in African Americans, and they might be approached by a research assistant to ask if they were willing to participate. The patient could return the card to the receptionist if the patient was not African-American and/or did not wish to be approached. Those who agreed to be screened completed the procedures in a private area of the clinic. The research assistant described the study and obtained verbal consent to complete a 10-minute depression screening interview in a private room. Patients who were positive on the first-stage depression screen completed full written study consent, and a research assistant arranged for the patient's medical visit to be audio taped.

Patients who screened positive for depressive symptoms in clinical sites were called at home within two weeks of their onsite screening to complete the second-stage screen (to determine whether they had a diagnosis of MDD by the Composite International Diagnostic Interview, or CIDI) with a 40-minute telephone baseline interview [29,30]. If they met diagnostic criteria, they were randomized according to their clinician's intervention assignment and told to expect a phone call from a depression care manager within a few days; interviewers also obtained respondents' consent to be called for 30-minute follow-up interviews at 6, 12, and 18 months from the baseline interview.

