Two other recruitment strategies supplemented the onsite approach. For these patient recruitment approaches, we obtained a waiver of HIPAA privacy authorization from the Johns Hopkins IRB and entered into agreements with the participating health plans to allow data sharing. The second recruitment approach was to have clinical managers at participating primary care sites help identify potential African-American study subjects using administrative and scheduling data. Field research staff then did onsite recruitment and screening at clinics where African-American patients were already scheduled to see a participating provider. The third patient recruitment approach was developed to meet requests from many participating clinicians that the study include some of their patients with known depression. Clinicians were asked to nominate 20 of their known African-American patient cases with MDD for possible inclusion in the study. Clinicians recommended patients with a broad spectrum of depression symptoms and in various stages of care. We sought and obtained IRB approval for clinicians to give research assistants patient contact information (*i.e*., name, address, phone number, and medical record number) for the purpose of preparing a letter that would be signed by the patient's clinician. Information packets containing the clinician's signed letter detailing the study goals and objectives and a prepaid study postcard that offered patients an option to refuse participation were sent to potential participants. Upon receipt of the letter, patients either called the study office, or, if no refusal postcard was received within two weeks of the mailing, they were called by study staff. In either case, during the telephone call patients were told about the study, asked questions to confirm eligibility, and asked if they would be willing to speak further about the study with a member of the study staff when they arrived at their next appointment. If they agreed, a field research assistant met the patient at the clinic prior to their next appointment. The research assistant administered the brief screening questionnaire, and the recruitment process proceeded as described above.

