The data on outcome variables fall into two broad categories: continuous variables, such as depressive symptom score (CES-D) [48] and functional status scores (MOS SF-12) [49], and dichotomous variables, such as depression remission status and receipt of guideline-concordant treatment. The primary ITT analyses are designed as regression modeling using patients as the unit of analysis, with each regression model structured to have a parameter designated for each visit where the outcome of the model was scheduled to be assessed, separately for each intervention group, so that the mean model is fully saturated for the intervention by visit parametrization. This parametrization allows estimation of mean differences observed within each intervention group betweeen baseline and a given follow-up visit for a continuous outcome, and odds ratios of having the outcome event at a given follow-up versus the baseline visit within each intervention group for a binary outcome, after adjusting for other covariates in the model. The evalution of patient-centered intervention effects will be conducted by testing the significance of difference of the adjusted mean differences, or the ratio of adjusted odds ratios, of a given follow-up versus the baseline visit between the intervention groups. The primary testing contrast is the baseline to 12-month change in outcomes between intervention groups; the models can easily accommodate additional data obtained by extending the follow-up to 18 months.

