#### Sample size considerations

One of the major hypotheses to be tested is that improvements in CES-D scores for depressed patients in the patient-centered intervention group will be greater than those in the standard intervention group. Previous studies of treatment of depression in primary care using similar interventions (excluding the patient-centered and cultural adaptations) have shown remission and symptom improvement differences between intervention and usual care groups of 20 to 30% [19,20]. Our resources and available recruitment pools allowed us to aim for 15 clinicians and 125 patients per group, with an average number of 8.3 patients per physician (cluster). By assuming a within-cluster or intra-class correlation of 0.1 [50] and 15% dropouts by the end of 12 months follow-up (reflected using the variance inflation factor), a correlation between the baseline and 12 month CES-D score of 0.5, a mean CES-D score of 30 points at baseline for both intervention groups, 25% score reduction (*i.e*., 7.5 points) by 12 months in the standard intervention group, and the common cross-sectional SD for CES-D of 10 points for both intervention groups at both visits, we would have 80% statistical power to detect a between-group difference of 3.6 points or more in improvement in mean CES-D score at one year using a two-sided test with Type I error of 0.05. That is, if we expect to see a 7.5 point improvement in mean CES-D score for the standard intervention group after one year, then we would have 80% power to detect a 11.1 points or greater improvement in mean CES-D score for the patient-centered intervention group after one year.

Ethics and Consent

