Limitations of the study should be discussed. The cluster design presents unique challenges with regard to comparability of groups (at the cluster and individual patient level), allocation concealment, maintenance of ITT principles, empty clusters, and participant switches from one cluster to another [55]. Several strategies have been recommended to overcome recruitment challenges: monitoring cluster guardian (*e.g*., practice leader) adherence to the study protocol before randomization of the cluster; including at least one patient participant before randomizing a cluster; and using recruiters who are blinded to participant allocation status. In this study, there was loss to follow-up among randomized clinicians before patient recruitment, which led to empty clusters (*e.g*., clinicians who did not contribute patients to the study) and failure to reach the recruitment target among patients, which may compromise the study's statistical power to detect differences in the primary outcome. Due to the staff resources available for recruitment and time frame needed for delivery of the clinician interventions, it was not feasible to delay randomization of clinicians until the first patient in each cluster was recruited. However, recruiters in this study were blinded to the allocation status of each cluster and its patients. With regard to analysis challenges, empty clusters and patients who switch from one cluster to another may lead to violation of the ITT principle. Recommendations include taking into account both clusters and individuals that withdraw or are lost to follow-up by using *ad hoc *missing data methods; keeping clusters as they were randomized, and using adjustment or propensity-score methods to deal with potential imbalances in both cluster and individual characteristics. In addition to these strategies, we will conduct sensitivity analyses to examine the potential impact of deviation from assumptions underlying such analytic approaches on the robustness of the study findings. Another design constraint is the limited ability to identify which aspects of the multi component interventions are most effective; we intend to conduct *post-hoc *analyses to determine whether the number of intervention contacts, use of intervention materials, and rating of intervention effectiveness by clinicians and patients are related to study outcomes.

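### Patient baseline appears to fall after clinician training, so change-from-baseline tests of patient-rated care lose whatever training effect is already present at enrollment

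*Protocol article*

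**What the plan says.** All references are to the protocol article.

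- **Order of events.** Clinicians were randomized first. The Discussion explains that "it was not feasible to delay randomization of clinicians until the first patient in each cluster was recruited", partly because of the time needed to deliver the clinician interventions.
- **Table 3 (clinician schedule).** "Audiotapes with 5 to 10 depressed patients" is marked in the post-intervention column only.
- **Table 4 (patient schedule).** The audiotapes have a single mark, at the enrollment visit. Footnote 7 says they were "collected at enrollment visit and after primary care provider intervention".
- **Recruitment strategies, Patients.** The visit on the screening day is taped. Screen-positive patients "were called at home within two weeks of their onsite screening to complete the second-stage screen", and that call includes the baseline interview.
- **Table 4, healthcare process and attitudes.** Participatory decision-making, visit-specific and overall satisfaction, and several attitude measures have an enrollment value.
- **Main outcome measures and statistical analysis plan.** Each arm has its own mean at every visit, and "The primary testing contrast is the baseline to 12-month change in outcomes between intervention groups". The same section describes the patient baseline measures as pre-intervention and adjusts all intention-to-treat analyses for variables found unbalanced.
- **Patient interventions.** The case manager first contacts the patient within a week after the baseline interview.

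**The concern.** The clinician component that separates the arms is communication training aimed at participatory decision-making. If a patient first rates decision-making and satisfaction after seeing a trained clinician, that rating may already be an outcome of the intervention. Subtracting it takes part of the effect out of the test.

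Aim three is the most exposed. It asks whether patients rate their care more highly, and these ratings are where training should show first. A real and lasting improvement could then be reported as no difference. The rule of adjusting for unbalanced baseline variables adds a second route to the same loss, because an imbalance produced by training would be treated as a chance imbalance.

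**Working it through.** **1. Timing.** Table 3 puts the patient tapes after the clinician intervention. Table 4 puts them at the enrollment visit and nowhere else. Both can hold only if the enrollment visit follows training. The dates allow this: clinicians enrolled from June 2004, patients were approached from October 2005, and the two detailing visits took about two months on average. The dates do not prove it for everyone. Clinician enrollment ran to March 2006 and so overlapped patient recruitment from October 2005. The description of patient measures as pre-intervention fits the case-manager component, but not the clinician component as scheduled in these tables.

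The article does not say which enrollment items were asked at the visit and which by telephone. Visit-specific satisfaction can only be rated after a visit.

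**2. What the contrast estimates.** Let D be the true between-arm difference at 12 months and f the share of it already present at baseline. Then

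expected change contrast = D − f·D = D(1 − f).

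With f = 0.5, half is lost. With f = 1 (immediate and stable), the expected contrast is 0. For binary outcomes the same holds on the log-odds scale. The documents give no value for f, so every value used here is an assumption.

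**3. Adjustment.** If an outcome is compared on level and adjusted for an enrollment rating that already differs by f·D, with regression slope b, the expected adjusted difference is D − b·f·D. Any positive b removes part of the effect. In the saturated longitudinal model a main-effect covariate largely cancels from the change contrast. The rule therefore matters most for level comparisons and for outcomes without an enrollment value.

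**4. Scale for CES-D.** The plan claims "80% statistical power to detect a between-group difference of 3.6 points or more in improvement in mean CES-D score at one year". Its inputs are SD 10, baseline-to-12-month correlation 0.5, intra-class correlation 0.1, 8.3 patients per clinician, 125 patients per arm, 15% dropout and a two-sided 0.05 test.

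- SD of change = 10·√(2(1 − 0.5)) = 10
- Design effect = 1 + (8.3 − 1)·0.1 = 1.73
- n per arm = 125·0.85 = 106.25
- Detectable difference = (1.960 + 0.842)·10·√(2·1.73/106.25) = 5.06 points

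The 3.6 is not reproduced. Dropping both clustering and dropout gives 2.802·10·√(2/125) = 3.54. That mismatch is a separate matter; 3.6 serves here only as a yardstick. Power on the plan's own basis is Φ(2.802(1 − f) − 1.960). The last column uses the recomputed standard error, 10·√(2·1.73/106.25).

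| Assumed f | Tested difference if D = 3.6 | Power, plan's 80% taken as given | Power, design effect 1.73 and 15% dropout |
|---|---|---|---|
| 0 | 3.60 | 80.0% | 51.4% |
| 0.10 | 3.24 | 71.3% | 43.5% |
| 0.25 | 2.70 | 55.6% | 32.1% |
| 0.50 | 1.80 | 28.8% | 16.8% |
| 1 | 0 | 2.5% | 2.5% |

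For CES-D the upper rows are the plausible ones. The baseline interview comes within two weeks of on-site screening, and the case-manager component has not begun.

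**The case against.** **Timing is inferred.** Footnote 7 covers audiotapes only, and its wording could describe two collection points. Nothing states that each clinician was trained before his or her first patient enrolled. This stands as a limit: a reader might infer that every baseline is post-training, and the text does not establish that. The single mark in Table 4 and the post-intervention entry in Table 3 still favor the post-training reading.

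**Not every rating is affected.** By the Table 4 footnotes, satisfaction with the case manager (6 and 12 months), ratings of care management and materials (12 months) and perceived involvement in care (18 months) have no enrollment value, so no change can be computed. The hypotheses for aim three are worded as higher ratings at follow-up, and the analysis section's examples are depression, function, remission and treatment. This narrows the point but does not remove it: that section gives no other test for process ratings that do have an enrollment value.

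**Baseline differencing protects against imbalance.** With 15 and 21 clinicians, eight of whom contributed no patients, a level comparison is more open to chance differences between clusters and in case mix. This stands, and it is why the change contrast should be kept and shown beside the level contrast.

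**Nominated patients.** "Clinicians were asked to nominate 20 of their known African-American patient cases with MDD" might be read as selection by clinicians who knew their arm. The article does not say when nominations were made relative to allocation. Nominees also passed the same screener and diagnostic interview, with recruiters masked. The risk is therefore conditional.

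**Conclusion.** The concern holds in a limited form. The patient baseline follows clinician randomization and, on the most natural reading of Tables 3 and 4, usually follows training and a visit with that clinician. This conflicts with calling patient measures pre-intervention. For participatory decision-making, visit-specific and overall satisfaction, and attitudes, the change contrast loses the fraction f of the effect already present at enrollment, up to all of it if the effect is immediate and stable. The documents do not allow f to be estimated.

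A reader might go further and conclude that the trial's tests cancel the clinician-training effect altogether, the primary outcome included. The documents do not support that. Only the part present at baseline is removed. Training effects that build later, and the whole case-manager component, remain in the contrast. For CES-D the loss is of unknown and probably small size.

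**What to change.** 1. Reconcile Tables 3 and 4, footnote 7 and the pre-intervention wording. State, by arm, how many patients enrolled after their clinician's training, and which enrollment items were asked before and after the visit.
2. For process and attitude ratings with an enrollment value, test the between-arm difference in level at 6 and 12 months, adjusting for site and for characteristics that training cannot affect. Show it beside the change contrast.
3. Report the enrollment rating by arm as a possible early effect of clinician training.
4. Keep these ratings out of the imbalance-driven adjustment set.
5. Add a 12-month-level sensitivity analysis for CES-D.
6. If nominations were made after clinicians knew their arm, add a sensitivity analysis without nominated patients.

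The cost is some wording and a few extra models on data already collected. The level contrasts are less precise and less protected against chance cluster or case-mix imbalance, so neither contrast should be shown alone. Excluding nominees would shrink a sample that already stands at 132 against a target of 250.
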